It is likely that some patients with primary Achilles tendon rupture need surgery and some are better off with non-operative treatment. This could be due to the individual morphology of the ruptured tendon and the potential to heal with good strength and a functionally acceptable length [13]. The identification and selection of patients for operative treatment has not yet been well investigated [14, 15]. The clinical criteria for recommending operative treatment differ and have not been derived from evidence. Some clinicians would recommend operative treatment for young patients with high functional demands and others would say that this should be avoided if the patient has a poor prognosis of healing based on comorbidities. These aspects clearly need to be taken into consideration but cannot stand alone. A quantitative and evidence-based measure or method is needed to guide the clinician for optimal treatment. Amlang et al. [14] have developed an ultrasonographic classification of Achilles tendon rupture but have not evaluated the length of the tendon or functional outcome after healing, and the method demands an experienced examiner. Barfod et al. have developed and validated the ultrasound-based Copenhagen Achilles Length Measure (CALM), which can be conducted in the emergency department as part of the primary diagnosis [16, 17]. Barfod et al. have also investigated the correlation of Amlang’s classification and CALM in the acute setting to functional outcome scores after 1 year in non-operative-treated acute Achilles tendon rupture. CALM was able to predict the final length of the tendon at one-year follow-up (manuscript in press). CALM is the base of the newly developed Copenhagen Achilles Rupture Treatment Algorithm (CARTA) together with examination of tendon overlap inspired by Amlang’s classification system [14], which may be used as a predictive tool for identifying patients at risk of critical elongation of the tendon after healing and poor functional outcome. A manuscript on CARTA has been submitted to a scientific journal.

Based on CARTA we propose an evidence-based, individualized algorithm for treatment of acute Achilles tendon rupture. The objective of this trial is to investigate if this algorithm is superior to both operative and non-operative treatment.

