### Primary outcome measure

The primary outcome is the heel-rise work test, which is an endurance test where the participant stands on one leg and lifts the heel up and down until exhaustion [18]. The number of heel rises is counted and the height measured and plotted into a diagram on the x-axis and y-axis, respectively. Based on the weight of the participant the total work is estimated as area under the curve. The heel lift distance between the heel and the floor is measured in millimeters. The procedure is performed on the uninjured leg first and subsequently on the injured leg at 12 months. The participant is barefoot for the heel-rise work test and stands on a flat surface with a 10° inclination. The measurement system MuscleLab (Ergotest Technology, Oslo, Norway) is used at all the centers for these functional tests. The tests are developed by the Gothenburg group [18]. The metric for both the primary outcome measure as well as all the secondary outcomes is value at time point, meaning that it is the difference at a point in time between groups that will be assessed. The method of aggregation (how data from each group will be summarized) will be equal for all three groups and will be either mean, median, percent, or proportion depending on the results.

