### Secondary outcome measures

The secondary outcome measures are listed below (the timing of the assessments is shown in Fig. 1).
Copenhagen Achilles Length Measure (CALM) [19] is an ultrasonographic measurement of tendon elongation. It comprises two measurements (Fig. 2): the total length of the Achilles tendon (free tendon and fascia) and the free length of the Achilles tendon. The measurements are preformed the same way; they have the same distal landmark but the proximal landmark differs. CALM has shown good reliability and is recommended over other measurements of elongation [17, 20, 21]. The measure is performed as described by Barfod et al. but with the feet of the patient (laying in the prone position) hanging free of the table instead of with 10° degrees of plantar flexion in the ankle joints as originally described [16, 21]. Landmarks are identified and marked on the skin. The distal landmark is the posterior and most superior part of the calcaneus in the midline, which on sagittal ultrasound examination is identified as the point where the cortical bone and its underlying shadow end. The proximal landmark for the total length of the Achilles tendon is the distal tip of the medial gastrocnemius head, which on sagittal ultrasound examination is recognized as the point where the most distal muscular fibers are inserted into the deep crural fascia. The proximal landmark for the free length of the Achilles tendon is the distal tip of the soleus muscle, which is defined at the point where the most distal muscular fibers insert into the Achilles tendon. The distance between these two points on the un-injured leg defines the total length of the Achilles tendon and the free length of the Achilles tendon, respectively. The differences between the non-injured and the injured leg are defined as tendon elongation. At inclusion only the total Achilles tendon length is measured for both legs. The examination of both the total and the free part of the tendon of both the injured and un-injured leg is performed at 6- and 12-month follow-up. The position of the feet also differs between inclusion and follow-up. During inclusion, the originally described position of the feet is used (10° of plantar flexion in the ankle joints) but during the 6- and 12-month follow-up, the feet hang free of the table.Heel-rise work test: The test is conducted as described for the primary endpoint and conducted as a secondary endpoint at 6 months.Achilles tendon resting angle (ATRA) [22]: ATRA is an indirect measurement of tendon elongation. The patient lies flat in the prone position on the examination bed. The knee is flexed at 90 degrees and the ankle sits in a relaxed position. The ATRA is determined as the angle between the longitudinal axis of corpus of the fibula and the longitudinal axis of corpus of the fifth metatarsus. ATRA is determined for both the injured and the uninjured leg. The difference between the healthy and the injured leg is evaluated. ATRA has shown excellent reliability [22, 23].Complications: Incidence rates of the commonly known complications and adverse events such as infection, re-rupture, permanent sural nerve dysfunction, deep venous thrombosis, adhesions, and pain at the scar are noted. Attention is also paid to unknown complications in relation to the treatments.Achilles tendon Total Rupture Score (ATRS) [24]: Patients fill out the ATRS questionnaire at inclusion and after 6 and 12 months in connection with the follow-up visits in the outpatient clinic. ATRS is a patient-reported outcome measure developed to assess symptoms and physical activity after treatment for acute Achilles tendon rupture. The Danish version was found to have good validity and be reliable to use for comparison on the group level [25].Tegner Activity Scale: A scale that aims to provide a standardized method of grading work and sporting activities. Tegner activity scale is a graduated list of activities of daily living, recreation, and competitive sports. The patient is asked to select the level of participation that best describes their level of activity at inclusion and at 6 and 12 months after rupture and before injury [26].Calf circumference: The patient sits on an examination bed with legs hanging down. The circumference of the calf is measured using a measuring tape (13 cm under apex patella).MRI: MRI of the calf is performed after 1 year for the first 60 patients included at Copenhagen University Hospital Amager-Hvidovre. MRI will be conducted to obtain a deeper understanding of changes to the different structures in the muscle–tendon complex during the first year after rupture. The MRI will be conducted at Copenhagen University Hospital Amager-Hvidovre in an Acanto 1.5 T scanner. Both lower legs will be scanned.Gait analysis: Gait analysis is performed after 6 and 12 months for the first 60 patients included at Copenhagen University Hospital Amager-Hvidovre. The gait analysis will be conducted at the Gait Laboratory, Copenhagen University Hospital Amager-Hvidovre. Twenty-two reflective markers are placed on the patient’s skin with tape on specific anatomical locations, as described by Speedtsberg et al. [27]. The participants are instructed to walk barefoot at a self-selected speed on a 10-m level walkway. The reflective markers are filmed by eight infrared cameras, whereby the joint angles during gait are measured. In combination with the ground reaction forces from two force plates embedded in the floor, the joint moments and powers will be calculated.

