**Fig. 3 Fig3:**
[figure not shown]
The Copenhagen Achilles Rupture Treatment Algorithm (CARTA) based on two ultrasonographic (US) examinations

Secondly, the elongation is measured by the CALM measure. Both legs are examined and the difference between the sides calculated as the elongation. The elongation is given in percentage of the length of the non-injured tendon. Patients with up to 7% elongation of the tendon are treated non-operatively and patients with 7% elongation or more are treated operatively. An elongation of 7% or more at time of injury can predict elongation of 10% or more at 1 year with a sensitivity of 77% and a specificity of 50% (paper submitted for publication). CALM is performed as previously described under outcome measures, but when used within the algorithm, the patient is positioned as described for the first part of the ultrasound examination.

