#### Analysis of endpoints

Demographic parameters will be presented for each treatment group with mean and standard deviation (SD) or median and interquartile range (IQR) for continuous parameters and frequencies and percentages for categorical parameters.

Difference in Heel-rise work test will be tested by *t*-test or, if data can’t be assumed to be normally distributed, Wilcoxon sum rank test. Test will be made for the comparison individual vs operative treatment and individual vs non-operative treatment. To account for possible confounders, a linear regression will also be fitted for each comparison. Confounders include, but are not limited to, sex, age, BMI, and ATRS pre-injury; the confounding effect of these variables will be evaluated in the model by including and removing the variable and evaluating the change between the treatment group estimates.

Differences in severe complications (yes/no) between individual and operative treatment will be tested by chi-square test or, if the amount of expected observations for a single combination is less than 5, Fishers exact test. Additionally, the test will be adjusted for possible confounders in a logistic regression model; possible confounders and evaluation of these will be done as described in the Heel-rise work test models. Similar tests and models are made for the comparison of individual and non-operative treatments. Differences between individual and operative treatment and individual and non-operative treatment for all other secondary outcomes will be tested by *t*-test or Wilcoxon sum rank test.

All analysis will be done as intention-to-treat (ITT), that is, each patient is analyzed according to the treatment group they are randomized to. The results will therefore be interpreted as the effect of offering the patient the specific treatment options, regardless of if they complete them or not. Missing data will be imputed by multiple imputation, with imputation models based on available variables believed to be predictive of the missing measures. Additionally, the analysis for the primary outcome will be conducted as per protocol analysis, with per protocol defined as patients complying with the assigned protocol.

No interim analyses will be done.

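### Elongation, Tegner and ATRS at follow-up are compared without adjusting for a baseline or pre-injury value that is collected; the tests are valid but give up some precision

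*Protocol article*

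**What the plan says.** The Analysis of endpoints section adds a linear regression to the heel-rise work comparison and a logistic regression to the severe-complications comparison. For the rest, differences between the individualized arm and each control "for all other secondary outcomes will be tested by *t*-test or Wilcoxon sum rank test". The Primary outcome measure section fixes what is compared: "The metric for both the primary outcome measure as well as all the secondary outcomes is value at time point". No baseline-adjusted analysis is stated for the remaining secondary outcomes.

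Three of those outcomes have an earlier value of their own:

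- **Total-length elongation.** Secondary outcome measures: "At inclusion only the total Achilles tendon length is measured for both legs". The side difference defines elongation, which is measured again at 6 and 12 months.
- **Tegner.** Patients report "their level of activity at inclusion and at 6 and 12 months after rupture and before injury".
- **ATRS.** "Patients fill out the ATRS questionnaire at inclusion and after 6 and 12 months". Pre-injury ATRS is also named in Analysis of endpoints as a covariate for the heel-rise work model, but not for ATRS itself.

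On elongation the article states that the early value is prognostic. Background: "CALM was able to predict the final length of the tendon at one-year follow-up". The CARTA section adds that 7% or more at injury predicts 10% or more at one year with sensitivity 77% and specificity 50%.

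**The concern.** In a randomized comparison of means, adjusting for an outcome's own baseline leaves the target difference unchanged and removes the part of the between-patient variance that the baseline explains. Leaving it out makes confidence intervals wider than the collected data require. The omission stands out most for elongation: it is the mechanism CARTA acts on and the first-listed secondary outcome, and treatment in the individualized arm is chosen on the very measurement that the comparison then ignores.

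Because the method is stated outright, this is a comment on a choice made and not on a detail left to an analysis plan. What is at stake is the precision of three secondary results.

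**Working it through.** **1. The article's own figure.** The Sample size section gives N = 2 × (1.96 + 1.281)² × 20² / 10² = 84.03, stated as 84 per group. It reproduces. It concerns heel-rise work only and is not affected.

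**2. Formula.** With correlation ρ between baseline and follow-up, adjustment multiplies the variance of the group difference by 1 − ρ². A comparison with 80% power unadjusted then has power Φ((1.96 + 0.842)/√(1 − ρ²) − 1.96). The 80% is a reference point; the article states no power for any secondary outcome.

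**3. Correlation for elongation.** The article gives no correlation. Assume that elongation at inclusion and at one year is bivariate normal, and that a proportion p exceeds 10% at one year. The test-positive rate is 0.77p + 0.50(1 − p) and the joint probability is 0.77p. Solving for ρ:

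| p (assumed) | ρ | variance removed |
|---|---|---|
| 0.2 | 0.398 | 15.8% |
| 0.3 | 0.419 | 17.6% |
| 0.4 | 0.431 | 18.6% |
| 0.5 | 0.437 | 19.1% |
| 0.6 | 0.436 | 19.0% |

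Taken at face value, this raises 80% power to 86–88%.

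**4. Allowing for surgery.** Background places the prediction work in non-operatively treated patients. In this trial one control arm is all operated, and CARTA operates on those with high inclusion elongation. A simple model shows the effect. All its inputs are assumptions, and it ignores the tendon-overlap criterion.

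- X is standardized inclusion elongation, with the cut-off at its mean.
- Without surgery, one-year elongation Y has variance 1 and correlation 0.42 with X.
- With surgery, Y is lowered by d and has correlation r with X.
- With m = E(X | X > 0) = 0.798, the CARTA arm has covariance (0.42 + r − md)/2, mean (−0.42m − d + rm)/2 and second moment 1 + (d² − 2mdr)/2. Its variance is the second moment minus the squared mean.
- The common slope b is the average of the two arms' covariances. The share of variance removed is 2b² / (V₁ + V₂), where V₁ and V₂ are the arm variances.

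Example, r = 0 and d = 0.5, CARTA vs non-operative: CARTA covariance (0.42 − 0.399)/2 = 0.011 and variance 0.951; b = (0.011 + 0.42)/2 = 0.215; share 2 × 0.215² / 1.951 = 4.8%.

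| r | d (SD) | CARTA vs operative | CARTA vs non-operative |
|---|---|---|---|
| 0 | 0 | 1.1% | 10.1% |
| 0 | 0.3 | 0.2% | 6.7% |
| 0 | 0.5 | 0.0% | 4.8% |
| 0.2 | 0 | 6.5% | 13.4% |
| 0.2 | 0.3 | 3.9% | 9.6% |
| 0.2 | 0.5 | 2.5% | 7.3% |
| 0.42 | 0 | 17.6% | 17.6% |
| 0.42 | 0.3 | 13.5% | 13.5% |
| 0.42 | 0.5 | 10.8% | 10.8% |

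Reference power of 80% becomes 80–87% against operative and 82–87% against non-operative treatment.

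**5. Tegner and ATRS.** No correlation is given, so ρ is assumed. At ρ = 0.3 the variance factor is 0.91 and 80% becomes 84%. At ρ = 0.5 the factor is 0.75 and 80% becomes 90%.

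**The case against.** The case against acting has four parts.

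**Validity.** Randomization makes the unadjusted tests valid, and chance baseline imbalance is already covered by the standard error. This stands. A reader might infer bias or an unsound comparison, but nothing in the article supports that.

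**Size for elongation.** A reader might apply the 16–19% reduction to both comparisons. The article does not support this. The prediction comes from non-operative care, whereas Operative treatment describes tensioning the tendon until its position matches the uninjured leg, and Safety expects more elongation without surgery. In the CARTA arm, the patients with the highest baseline are the ones whose tendon is repaired, which flattens the slope. The Discussion also admits a sizeable individual measurement error for CALM. So 16–19% is a ceiling, and the gain against operative treatment may be close to nil. This stands.

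**What is estimated.** Adjustment keeps the target unchanged for a mean difference. Tegner is ordinal, and the article allows a rank test and leaves mean or median open. If the rank test were the main analysis, a linear model would change what is reported. This is a reason to keep the rank test alongside.

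**Whether the elongation baseline is usable.** Foot position differs between inclusion and follow-up. That makes a change score hard to interpret but does not bar use as a covariate; it may lower the correlation. Also, Secondary outcome measures reads as an inclusion scan for everyone, whereas Table 1 mentions the ultrasound only for the individualized arm and places it at the same visit as randomization, with no stated order. A scan in all arms before allocation is therefore likely but not spelled out.

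**Conclusion.** The point holds as a minor efficiency matter on three secondary outcomes. The stated method leaves out information that the article says is collected, and for elongation says is prognostic.

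- **Elongation:** roughly 0 to 18% of the variance against operative and 5 to 18% against non-operative treatment. This rests on a non-operative correlation of 0.42, an operated correlation of 0 to 0.42 and a surgical effect of 0 to 0.5 SD, all but the first purely assumed.
- **Tegner and ATRS:** 9 to 25%, resting entirely on an assumed correlation of 0.3 to 0.5.

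The point does not extend to free tendon length, ATRA, calf circumference or the 6-month heel-rise test, for which no baseline is stated. Nor does it touch the primary analysis, which has its own adjusted regression, or the sample size, which reproduces.

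**What to change.** For total-length elongation, Tegner and ATRS at 6 and 12 months, prespecify a linear regression of the follow-up value on group for each of the two planned comparisons. Enter the outcome's own earlier value as a fixed covariate: inclusion total-length elongation, pre-injury Tegner and pre-injury ATRS. The covariate should not go through the include-and-remove check planned for confounders. Report the adjusted mean difference with its confidence interval, and keep the t-test or Wilcoxon test as a supporting analysis, particularly for Tegner.

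Use the inclusion scan only as a covariate, never in a change score, and state that it is taken in all arms before allocation. If that is not so, the elongation part of this change should be dropped.

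The cost is a few sentences in the analysis section and, provided the scan is done in all arms, no new data. Recall error in pre-injury scores and the different foot position at inclusion will reduce the gain.

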### Safety

#### Risks and side effects

All participants in the study are at risk of developing pressure wounds from the functional brace and cast and a small risk of developing adhesion of the tendon to the skin. For participants receiving non-operative treatment there is a higher risk of re-rupture and an expected relatively higher risk of elongation of the injured Achilles tendon and inferior muscular force in the plantar flexion over the ankle joint compared to the patients receiving operative treatment. For the participants receiving operative treatment there is a risk of infection in the operative wound and temporary or permanent damage to the sural nerve.

The only possible need of modifying the allocated intervention for a given trial participant is if a participant treated non-operatively has insufficient healing after 12–16 weeks after injury or experiences a trauma re-injuring the tendon during the healing phase. In these situations, surgery is most often needed.

All participants are covered by the hospitals insurance during the treatment period.

#### Education and training

Observations and measurements are carried out by trained personnel at the orthopedic department or by trained sports physiotherapists at the participating centers. Follow-up evaluations are performed by the project physiotherapists, who are blinded to the initial treatment of operative or non-operative treatment (at all centers beside one where the physiotherapists see the patients all the time) until performing CALM, where the presence of a surgical scar is evident. The second author will also conduct test calibration once a year of the outcome measures within the doctors and physiotherapists that are involved in data collection.

#### Adverse events

In this context, adverse events are defined as any unintended, unfavorable finding, symptom, or disease that occurs, whether or not it is likely to be related to the study. All adverse events will be recorded, and special attention is paid to sural nerve damage, re-rupture rate, deep venous thrombosis, and both superficial and deep infections. Healing of the tendon in an elongated length is not considered an adverse event but is a primary endpoint of the study.

#### Critical adverse events

In this context, a critical adverse event is defined as an event or reaction which will cause death, life-threatening situations, hospitalization or prolongation of existing hospitalization, or permanent or severe disability, including an unacceptably high incidence of sural nerve damage.

An investigator assesses whether there is a reasonable possibility that the critical adverse event is possibly correlated with the trial’s modified treatment. The following factors are included in the assessment: consistency in time, consistency with the known effects of treatment, and alternative causes.

If a critical adverse event is considered to have a causal relationship with the treatment, then the project manager, those clinically responsible, and the other investigators will evaluate whether the study should be terminated.

